## Abstract

**Objective:**

To evaluate the effectiveness and safety of Xiao’er Fengreqing Oral Liquid (XFOL) for pediatric acute pharyngitis/tonsillitis (external wind heat syndrome) through a multi-center, randomized, double-blind, positive-controlled, non-inferiority clinical trial.

**Method:**

A total of 120 participants (60 per group) will be randomized to receive either XFOL or Xiao’er Yanbian Granules (positive control) for 5 days. The primary outcome is the throat pain resolution rate and overall effective rate at Day 5, assessed via the Wong-Baker Faces Pain Rating Scale (WBS). Secondary outcomes include time to symptom onset/resolution, fever resolution time, and traditional Chinese medicine (TCM) syndrome scores. Safety assessments will monitor adverse events, vital signs, and laboratory parameters. Statistical analyses will follow a pre-specified plan, employing non-inferiority testing, survival analysis for time-to-event endpoints, and generalized estimating equations for repeated measures. Missing data will be handled using the last observation carried forward (LOCF) method for effectiveness endpoints, while safety analyses will rely on observed cases.

**Conclusion:**

This trial will provide rigorous evidence on the non-inferiority and safety profile of Fengreqing Oral Liquid, supporting its integration into pediatric care for acute upper respiratory infections. Adherence to a predefined statistical analysis plan ensures transparency and minimizes bias, ultimately guiding evidence-based clinical practice for TCM interventions.

## Introduction

Pediatric acute pharyngitis/tonsillitis (PAPT) is an inflammatory condition of the upper respiratory tract, primarily affecting the pharyngeal mucosa and tonsils, with symptoms including sore throat, fever, dysphagia, and cervical lymphadenopathy (Van Driel et al., 2021). Viral pathogens account for 70%–80% of cases, while Group A *Streptococcus* (GAS) is the predominant bacterial cause, responsible for 15%–30% of cases in children aged 5–15 years (Le Marechal et al., 2013). Globally, PAPT represents a major pediatric health burden, contributing significantly to outpatient visits and antibiotic prescriptions (Carapetis et al., 2005). In high-income countries, the annual incidence ranges from 60 to 90 per 1,000 children, peaking during colder months (Spinks et al., 2021). In the U.S., cross-sectional studies have demonstrated that both acute and chronic tonsillitis contribute significantly to pediatric healthcare burden, with chronic cases requiring more frequent office visits and higher prescription medication use compared to acute cases (Duarte et al., 2015).

Current management of PAPT prioritizes accurate diagnosis to avoid unnecessary antibiotic use while preventing complications such as rheumatic fever. International guidelines, including those from the Infectious Diseases Society of America (IDSA) and the American Academy of Pediatrics (AAP), recommend rapid antigen detection tests (RADTs) or throat cultures to confirm GAS infection before initiating antibiotics (Wald et al., 2013; Shulman et al., 2012). First-line therapy for confirmed GAS pharyngitis remains oral penicillin or amoxicillin due to their narrow spectrum and cost-effectiveness (Van Driel et al., 2021). However, antibiotic overprescription persists globally, with studies reporting 60%–70% of viral cases receiving antimicrobials, exacerbating resistance rates for *Streptococcus* pneumoniae and *Haemophilus* influenzae (Klein et al., 2024). Macrolides and cephalosporins are reserved for penicillin-allergic patients, though emerging resistance to these agents has been documented in Asia and Europe (Klein, 1997). Nonsteroidal anti-inflammatory drugs (NSAIDs) and acetaminophen are widely used for symptomatic relief, but their overuse in children raises concerns about renal and hepatic toxicity (Fashner et al., 2012). Novel strategies, including GAS vaccines targeting M-protein epitopes and phage therapy (Wang et al., 2018), are under investigation but face challenges in effectiveness and scalability.

Emerging evidence supports the role of traditional Chinese medicine (TCM) in managing PAPT, particularly for viral or mild bacterial cases. Xiao’er Fengreqing Oral Liquid (XFOL), a 20-herb formulation including Lonicerae Japonicae Flos (honeysuckle), Forsythiae Fructus (forsythia), and Menthae Haplocalycis Herba (mint), among others, has demonstrated anti-inflammatory, antiviral, and immunomodulatory properties (Zhou et al., 2020). Produced by Handan Pharmaceutical Co., Ltd. (Handan, China), XFOL has been approved by the National Medical Products Administration of China for marketing (Z19990012) in 1995. A multicenter randomized controlled trial (RCT) comparing XFOL with Xiao’er Baotaikang Granules (control) showed comparable effectiveness in fever resolution (median time: 46 h vs. 46 h, P = 0.83) but superior improvement in nasal obstruction (55.95% vs. 39.18%, P < 0.05) and pharyngeal erythema (70.09% vs. 47.62%, P < 0.01) at Day 3 (Feng and Du, 2020). Another trial (n = 65) reported 88.33% clinical cure rates for influenza A-associated pharyngitis with XFOL, achieving viral clearance in 100% of per-protocol cases without severe adverse events (Zhou et al., 2020). Mechanistic studies attribute its effects to inhibition of NF-κB signaling and downregulation of pro-inflammatory cytokines (IL-6, TNF-α) (Jia et al., 2021). Despite promising results, the reliability of these conclusions is reduced due to the low methodological quality of the original studies. Moreover, existing studies lack data from positive-controlled trials. To address this evidence gap, we designed a non-inferiority randomized controlled trial and selected Xiao’er Yanbian Granules (XYG) as the positive control drug due to its proven efficacy in reducing tonsillar inflammation, inflammatory markers (IL-4, IL-1β, TNF-α, CRP), and symptom duration in pediatric pharyngotonsillitis (Wen et al., 2024). Using a non-inferiority margin of Δ = 0.1, based on previous non-inferiority clinical studies and the endorsement of clinical experts, this study will objectively validate XFOL’s effectiveness and safety in PAPT.

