#### Sample size calculation

Primary endpoints: throat pain resolution rate and overall effective rate

Parameters: Expected throat pain resolution rate: 91.43% (intervention group) vs. 76.92% (control group), non-inferiority margin (Δ) = 0.1 (Zhu et al., 2014), one-sided α = 0.025, power (1-β) = 80% (Chow et al., 2017). Initial calculation using PASS 15 software yielded 34 participants per group.

Adjustments:

A 20% dropout rate adjustment (n = 34/0.8 ≈ 43) required 44 participants per group (total 88).

To account for potential challenges in pediatric compliance and ensure robust statistical power, the final sample size was increased to 120 participants (60 per group). Since non-inferiority must be demonstrated for both primary endpoints to consider the trial successful, no adjustment for multiple testing is required in the analysis phase.

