### Analysis of primary outcome

Non-inferiority will be evaluated using a predefined margin (Δ = 10%), with the lower bound of the one-sided 97.5% CI for the risk difference (trial-control) between groups compared against −Δ. If this lower bound exceeds −Δ, non-inferiority will be established. The sample size was calculated based on this non-inferiority hypothesis with a one-sided significance level of 0.025, maintaining consistency between design and analysis phases. Between-group comparisons will utilize Chi-square tests for categorical outcomes, supplemented by mixed-effects logistic regression adjusted for baseline covariates (age, baseline WBS score). To ensure consistency in statistical inference, both FAS and PPS analyses must demonstrate non-inferiority to confirm the robustness of conclusions. The trial will be considered successful only when non-inferiority is established for both primary endpoints; therefore, no adjustment for multiple testing is necessary as this represents a conservative approach requiring success on all endpoints. Should non-inferiority be established, superiority testing will be conducted as a hierarchical testing procedure by assessing whether the lower bound of the 95% CI exceeds zero. Results will be reported as proportions, risk differences, and adjusted odds ratios with 95% CIs, with forest plots used to visually represent the treatment effects and their confidence intervals relative to both the non-inferiority margin and zero.

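### A 10-point non-inferiority result against XYG is said to validate XFOL's effectiveness, but the article states no link between that margin and any XYG effect on the Day 5 endpoints

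*Protocol article*

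**What the plan says.** The Introduction gives the margin's basis as "Using a non-inferiority margin of Δ = 0.1, based on previous non-inferiority clinical studies and the endorsement of clinical experts" and finishes the sentence with the aim that "this study will objectively validate XFOL’s effectiveness and safety in PAPT". XYG was chosen as control for its "proven efficacy in reducing tonsillar inflammation, inflammatory markers (IL-4, IL-1β, TNF-α, CRP), and symptom duration in pediatric pharyngotonsillitis". No effect size, comparator or Day 5 WBS rate accompanies that statement.

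The section Sample size calculation gives "Expected throat pain resolution rate: 91.43% (intervention group) vs. 76.92% (control group), non-inferiority margin (Δ) = 0.1", with a literature citation after the margin.

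Under Analysis of primary outcome, the lower bound of the one-sided 97.5% interval for the risk difference (XFOL minus XYG) is compared with −10 points: "If this lower bound exceeds −Δ, non-inferiority will be established". Both primary endpoints (WBS of 0, and at least a 50% fall in WBS, at Day 5) must pass, in both the FAS and the PPS. Superiority is a later step and is not needed for success. Under Intervention, each arm receives one active product plus the placebo of the other, so no child is on placebo alone.

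**The concern.** The primary analysis uses one contrast, XFOL against XYG. That contrast shows XFOL to be effective only if XYG itself raises the Day 5 rates by more than the margin over the natural course. Earlier non-inferiority trials and expert endorsement can support a statement that 10 points is an acceptable loss against XYG. They do not supply XYG's effect over nothing, which a claim of effectiveness needs.

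The setting makes this more than a formality. Symptoms began within 48 hours of entry, suspected bacterial cases are excluded, and the endpoint is at Day 5, so substantial recovery without treatment is plausible, though the article gives no figure. A positive result could then come from two products that both work or from two that add nothing, and the rule cannot tell these apart. At stake is what the trial may conclude, in an article that looks ahead to use in pediatric care.

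**Working it through.** **1. The plan's own figure.** Inputs from Sample size calculation: XFOL 0.9143, XYG 0.7692, margin 0.10, "one-sided α = 0.025, power (1-β) = 80" per cent. With unpooled variance:

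n = (1.960 + 0.842)² × (0.9143×0.0857 + 0.7692×0.2308) / (0.1451 + 0.10)² = 7.85 × 0.2559 / 0.0601 = 33.4, so 34 per group.

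This agrees with "Initial calculation using PASS 15 software yielded 34 participants per group". The arithmetic is not in question. It assumes XFOL to be 14.5 points better than XYG and uses nothing about XYG against no treatment.

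**2. The test at its own null.** With XFOL exactly 10 points below XYG, 60 per arm and control rates from 60% to 95%, the single-endpoint rule is met about 2.1% to 3.7% of the time. It is near nominal for the hypothesis that it tests.

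**3. Margin against XYG's effect.** XYG's effect on resolution is 76.92% minus the untreated rate. It is no larger than the margin once the untreated rate reaches 76.92 − 10 = 66.92%. For assumed untreated rates:

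| Untreated rate | XYG's whole effect (points) |
|---|---|
| 60% | 16.9 |
| 65% | 11.9 |
| 70% | 6.9 |
| 75% | 1.9 |

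**4. Chance of success if both products are inert.** Both arms then share one true rate p. For one endpoint and one analysis set, approximately:

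P = Φ(0.10 / √(2p(1−p)/n) − 1.96)

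At p = 0.7692 and n = 60, the standard error is √(2×0.7692×0.2308/60) = 0.0769, so P = Φ(1.300 − 1.960) = 0.255. Exact enumeration gives 0.268 with a Wald bound and 0.264 with a Newcombe bound.

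The plan's rule is stricter: both endpoints and both analysis sets must pass. It was simulated with resolution nested within effectiveness, 60 per arm in the FAS, and a PPS of 48 per arm drawn at random from it. The 48 is an assumption, 60 × 0.8, which borrows the plan's 20% dropout.

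| Resolved / effective, same in both arms | FAS only (Wald / Newcombe) | FAS and PPS both pass (Wald / Newcombe) |
|---|---|---|
| 50% / 80% | 12% / 11% | about 7% / 7% |
| 76.92% / 90% | 21% / 19% | 13% / 12% |
| 85% / 95% | 32% / 27% | 23% / 17% |

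All rates are assumptions as natural-course rates. The middle row is the one anchored to the plan: if XYG is inert and its expected 76.92% is right, then 76.92% is the natural-course resolution rate. The plan states no expected effective rate.

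**The case against.** **The margin may have a sound derivation elsewhere.** The sample size section attaches a source to it, the Introduction cites another for XYG, and a journal article condenses a fuller protocol. This stands in part. A reader might infer that no link to XYG's effect exists; the article supports only that it states none. Shorter symptom duration, one of the XYG benefits named, also bears on the proportion resolved by a fixed day. But no size or reference treatment is given, and the basis that the article does state does not carry the claim made in the same sentence.

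**The overclaim is local.** The Abstract's conclusion speaks of non-inferiority, the Discussion of efficacy relative to the comparator, and the Conclusion only of evaluating. This stands: the Introduction's sentence is the main place to change.

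**The risk is easily exaggerated.** This also stands. A reader might infer that two inert products would pass more often than not. That needs untreated resolution rates well above the 76.92% that the plan expects under XYG, and it ignores the requirement that FAS and PPS both pass. The 85% row already exceeds the plan's control rate and shows only the direction.

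**Stronger remedies are tempting.** A reader might ask that effectiveness be claimed only if XFOL beats XYG. At the plan's rates, power for superiority on resolution is Φ(0.1451/√(0.2559/60) − 1.96), about 60% (51% with 48 per arm), and an XFOL truly equal to an effective XYG would rarely qualify. That is a debatable trade-off, not a correction. Comparing the arms at Day 3 would not help either, because two inert products would look alike then too.

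**Conclusion.** The point holds as one about what the trial may conclude. Non-inferiority with this margin supports a statement relative to XYG. On the basis given, it does not by itself validate XFOL's effectiveness. If neither product worked, the full rule would still be met roughly 7% to 23% of the time across the scenarios shown, and 12–13% at the plan's own control resolution rate, against a nominal 2.5% that refers to a different error.

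These figures rest on assumed natural-course rates, an assumed effective rate, and a PPS of 48 per arm lost at random. They do not show that the test is miscalibrated, that XYG is ineffective or that the sample size is wrong.

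**What to change.** In the Introduction, and in any conclusion drawn from the primary non-inferiority rule, replace the statement that the study validates XFOL's effectiveness with: *the study will show whether XFOL's Day 5 resolution and effective rates are not more than 10 percentage points below those of XYG*. Add: *without a placebo arm, or a margin derived from XYG's effect over placebo on these endpoints, non-inferiority alone does not establish that XFOL is effective.*

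The Discussion's relative wording already points this way. The change needs no extra participants, visits or analyses. Its cost is a narrower headline claim if only non-inferiority is shown.

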## Methods

### Ethical approval

This trial was approved by the ethics review committee of the Beijing University of Chinese Medicine Third Affiliated Hospital (ECPJ-BZYSY-2024-03, Beijing, China), and obtained ethical approval from each sub-center. All participants will sign a written informed consent form prior to enrollment. The development and reporting of the trial protocol adhere to the Consolidated Standards of Reporting Trials (CONSORT) 2010 Statement (Schulz et al., 2010). The trial has been registered in International Traditional Medicine Clinical Trial Registry (ITMCTR2024000569).

### Trial design

This trial employs a multi-center (three-centers), randomized, parallel-group, non-inferiority design. Eligible participants, after signing written informed consent, will be randomly assigned in an equal ratio to either the trial group or the control group. Enrolled participants will receive medication for a 5-day treatment duration. After completing 5 ± 1 day of continuous medication, participants will return to the hospital for follow-up, return the study medication and diary cards, and terminate treatment. The flowchart of the trial design is presented in Figure 1.

**FIGURE 1 F1:**
[figure not shown]
Flowchart of the trial design. XFOL, Xiao’er Fengreqing Oral Liquid; XYG, Xiao’er Yanbian Granules.

### Participant and public involvement

Suggested: No participants or members of the public were involved in the design or conduct of this trial.

### Diagnostic criteria

#### Standard medicine criteria

The diagnosis of acute pharyngitis and tonsillitis follows established guidelines (Chinese Association of Traditional Chinese Medicine, 2020; Hu, 2015; Liu and Gu, 2017; Zheng, 2002). Acute pharyngitis requires: (1) acute-onset sore throat with dysphagia; (2) pharyngeal mucosal hyperemia, swollen lymphoid follicles, or scattered purulent spots; (3) predisposing factors (e.g., viral/bacterial exposure, environmental irritants). Acute tonsillitis is defined by: (1) systemic symptoms (fever ≥38°C, chills, fatigue); (2) severe odynophagia with tonsillar erythema/swelling (Brodsky scale Grade I-III); (3) laboratory evidence (elevated WBC, neutrophils, or CRP for bacterial cases). Infants may present atypically with drooling, abdominal pain, or respiratory distress.

#### TCM syndrome differentiation

External wind-heat syndrome is diagnosed per TCM guidelines (Chinese Association of Traditional Chinese Medicine, 2020; Zheng, 2002), requiring:

Core features: (a) acute sore throat aggravated by swallowing; (b) erythematous pharynx/tonsils without suppuration.

Supporting signs: Fever (≥37.8°C), dry throat, yellow sputum, rapid floating pulse, red tongue with thin yellow coating.

Exclusion criteria: Purulent tonsils, thick greasy tongue coating, or deep pulse indicating heat-toxin or dampness patterns.

#### Diagnostic confirmation

The diagnosis is confirmed if the participant presents with one main symptom, one pharyngeal sign, at least two secondary symptoms, and the corresponding tongue and pulse signs.

#### Inclusion criteria

Eligible participants must satisfy all criteria:

Age 3–12 years, either sex.

Meeting the above diagnostic criteria for external wind heat syndrome.

Symptom onset within 48 h prior to enrollment.

No use of antipyretics, antibiotics, or antiviral drugs within 24 h before enrollment.

Legal guardian provides written informed consent and agrees to standardized follow-up.

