#### Exclusion criteria

Participants are excluded if any of the following apply:

Alternative diagnoses: (1) Suspected bacterial infection (e.g., tonsillar exudate, cervical lymphadenitis, or fever ≥39.5°C). (2) Herpangina, hand-foot-mouth disease, or other viral exanthems.

Comorbidities: (1) Chronic pharyngitis/tonsillitis (>3 episodes/year). (2) Immunodeficiency, asthma, or severe cardiopulmonary diseases.

Medication factors: (1) Allergy to XFOL components or control drug (e.g., Lianhua Qingwen granules). (2) Use of immunosuppressants or systemic corticosteroids within 4 weeks.

Logistical contraindications: (1) Participation in other clinical trials within 30 days (2) Inability to comply with protocol (e.g., language barriers, geographic instability).

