#### Rescue therapy

Acetaminophen oral suspension (brand name: Tylenol; 100 mL:3.2 g) will be administered as antipyretic rescue medication for participants with axillary temperature ≥38.2°C (Liu and Gu, 2017). For dosage, 1–3 years (12–15 kg): 3 mL per dose; 4–6 years (16–21 kg): 5 mL per dose; 7–9 years (22–27 kg): 8 mL per dose; 10–12 years (28–32 kg): 10 mL per dose. For frequency, repeat every 4–6 h if fever persists, with a maximum of 4 doses within 24 h. Persistent high fever unresponsive to rescue therapy requires immediate medical intervention.

During the trial, the use of antibiotics, antiviral agents, or other TCM with purported effectiveness for pediatric acute pharyngitis/tonsillitis is strictly prohibited. Additionally, non-protocol treatments such as infrared therapy, cupping, and acupuncture are disallowed throughout the study and follow-up periods. Acetaminophen is permitted for fever management (axillary temperature ≥38.2°C), and its dosage must adhere to the product instructions. All concomitant medications, including rescue therapies, must be meticulously documented in the CRF and original medical records, specifying the generic drug names, dosages, administration times, and reasons for use to ensure comprehensive data integrity and protocol adherence.

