#### Baseline data

Prior to treatment initiation, comprehensive baseline data will be collected, including demographic characteristics (sex, age, height, weight, ethnicity), medical history (disease duration, past medical conditions, allergies, pre-trial medications), and diagnostic indicators (symptoms such as sore throat and fever, physical signs including pharyngeal/tonsillar erythema, and laboratory results).

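### The 24 h pre-enrolment washout leaves out the TCM class that the protocol bans during the trial, so children just treated with XFOL, XYG or a similar product can enrol and may dilute the non-inferiority contrast

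*Protocol article*

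**What the plan says.** Under Inclusion criteria, all of which must be met, the rule on recent medication is "No use of antipyretics, antibiotics, or antiviral drugs within 24 h before enrollment", alongside "Symptom onset within 48 h prior to enrollment". Apart from allergy to the study products, the only medication-based item under Exclusion criteria is "Use of immunosuppressants or systemic corticosteroids within 4 weeks".

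The Rescue therapy section states that "the use of antibiotics, antiviral agents, or other TCM with purported effectiveness for pediatric acute pharyngitis/tonsillitis is strictly prohibited". That sentence limits its scope at the start: "During the trial, the use of antibiotics, antiviral agents, or other TCM".

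Prior medication is collected at baseline as part of "medical history (disease duration, past medical conditions, allergies, pre-trial medications", and the section on demographic and baseline characteristics summarises it by arm. It has no other stated use. The primary model is "mixed-effects logistic regression adjusted for baseline covariates (age, baseline WBS score", and the subgroups are age and baseline pain severity.

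**The concern.** The on-treatment ban names three drug classes: antibiotics, antivirals and TCM active in this condition. The washout covers the first two and omits the third, which is the class both study products belong to. The Introduction says XFOL is approved for marketing, and the Control group section gives XYG a national approval number, so prior use is possible. A site following the text would enrol a child who had taken either product for up to two days for this episode.

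Prior exposure of this kind, shared by both arms, tends to make the arms look alike. Non-inferiority is declared when the lower confidence bound for the risk difference lies above −10 points, so shrinking a true deficit moves the result towards the claim. The per-protocol analysis gives no protection, because a pre-treated child who meets the criteria has not deviated from the protocol.

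**Working it through.** **Side by side**

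| Drug class | Washout (Inclusion criteria) | Ban during trial (Rescue therapy) |
|---|---|---|
| Antibiotics | yes, 24 h | yes |
| Antivirals | yes, 24 h | yes |
| TCM active in this condition | not named | yes |

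No other section closes the third row.

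**Inputs from Sample size calculation.** "Expected throat pain resolution rate: 91.43% (intervention group) vs. 76.92% (control group"; margin 0.10; one-sided α 0.025; power 80%; final size 60 per arm.

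**Reproducing the plan's figure**

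n = (1.960 + 0.842)² × [0.7692 × 0.2308 + 0.9143 × 0.0857] / (0.1451 + 0.10)² = 7.849 × 0.2559 / 0.0601 = 33.4, so 34 per arm, as stated. The formula below is therefore on the plan's own footing.

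**Dilution model (assumed)**

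- f is the share pre-treated in each arm. The documents do not give it; 10% to 30% is an assumed range.
- c is the fraction of the true difference that pre-treatment removes in those children. The documents do not give it; c = 1 is the upper bound.
- The control rate stays at 0.7692.
- Difference seen = d × (1 − c·f), where d is the true difference.
- P(non-inferiority) = Φ( [d(1 − c·f) + 0.10] / SE − 1.96 ), with SE = √[ pC(1 − pC)/60 + pT(1 − pT)/60 ].

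Worked case, d = −0.10, f = 20%, c = 1: the difference seen is −0.08, so pT = 0.6892. SE = √[(0.1775 + 0.2142)/60] = 0.0808. Then 0.02/0.0808 = 0.2475, and Φ(0.2475 − 1.96) = 4.3%.

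**Results, resolution endpoint alone, 60 per arm**

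| f | False non-inferiority, d = −10 points, c = 1 | Same, c = 0.5 | Power, d = +14.51 points, c = 1 |
|---|---|---|---|
| 0 | 2.5% | 2.5% | 96.4% |
| 10% | 3.3% | 2.9% | 93.2% |
| 20% | 4.3% | 3.3% | 88.7% |
| 30% | 5.6% | 3.8% | 82.6% |

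With 48 per arm (60 less 20% dropout) and c = 1, the false-positive figures are 2.5%, 3.2%, 4.1% and 5.2%.

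**The case against.** The gap in the text is hard to dispute; its consequence is open to several objections.

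- **Short exposure.** The 48 h onset limit caps pre-treatment for this episode at two days, and five days of randomised treatment follow before the Day 5 endpoint. Nothing shows that two days of prior TCM would erase the whole difference. This stands, and it is why c = 1 is only an upper bound.
- **Still symptomatic at entry.** Diagnostic confirmation requires a main symptom, a pharyngeal sign and at least two secondary symptoms, so a child largely cleared by earlier TCM would not qualify. This limits the effect but does not remove it.
- **Both directions.** Dilution favours the claim only if XFOL is worse. At the planning rates it costs power instead. This stands, and both are shown.
- **Joint success rule.** Both endpoints must pass in both analysis sets, so the trial-level error cannot exceed the error for resolution alone. This stands.
- **Data exist.** Pre-trial medications are recorded and summarised by arm. This makes a sensitivity analysis possible, but none is specified and eligibility is unaffected.
- **Condensed article.** A fuller protocol might add the class. However, the criterion as printed names its drug classes and reads as complete.

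A reader might also infer several stronger points that the documents do not support. Prior use should not bias one arm against the other, because randomisation should balance it. The trial does not compare mixed treatments throughout the course, because other TCM is banned during it. A lower baseline pain score does not alter the resolution endpoint, which requires a score of 0, and the supplementary model adjusts for baseline score. Finally, the Rescue therapy section gives no reason for its ban, so confounding cannot be cited as the protocol's own motive.

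**Conclusion.** The inconsistency is real. The washout omits a class that the protocol prohibits on treatment, and children recently given either study product are eligible and analysable. If carry-over exists, it dilutes the contrast.

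With a true deficit of exactly 10 points, the false-positive rate on resolution would rise from 2.5% to between 2.9% and 3.8% if pre-treatment removes half the difference, and to at most 3.3% to 5.6% if it removes all of it, for an assumed 10% to 30% pre-treated. If XFOL is better at the planning rates, full dilution costs about 3 to 14 points of power. These figures illustrate the mechanism and are not estimates, because neither prevalence nor carry-over is documented. It would go too far to say that carry-over will pull the arms together: the onset limit and the Day 5 endpoint may keep the effect modest. The point is still worth acting on, because the remedy is simple and helps the trial whichever way the true difference lies.

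**What to change.** Reconcile Inclusion criteria with Rescue therapy. Add to the pre-enrolment criterion TCM products held to work in acute pharyngitis or tonsillitis, naming XFOL and XYG. The trial team should set the window; the existing 24 h is the minimum consistent with the other classes.

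For children already enrolled, identify prior users from the recorded pre-trial medications, blind to allocation, and repeat the primary non-inferiority analysis without them as a sensitivity analysis.

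The cost is one line of protocol text and one extra analysis, with no new data collection and no change to the sample size calculation. Screen failures will rise in proportion to prior TCM use. If such use is common enough to matter for dilution, the effect on recruitment could also be material.
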